#### Quaternary Hypothesis

The quaternary hypothesis is that the display of predictive analytics monitoring reduces costs to the health system.

We will determine whether the display of predictive analytics is cost-effective to the health care system. Collection of end points to understand trade-offs and potential burdens, consequences, and advantages for this platform from the clinician perspective is critical and presents novel knowledge. Additionally, we can form an estimate for not only the cost of intervening but also the overall costs of implementing a predictive analytics or AI monitoring platform within a health system using multiple criteria (Table 1).

We will conduct an economic cost-effectiveness analysis comparing the clinical outcomes and associated cost of care between the intervention and usual care group. We will use a Markov decision tree and Monte Carlo simulation to examine the impact of CoMET compared with usual care from a health system perspective. We will measure incremental effect as the in-hospital mortality difference and the number of quality-adjusted life years gained discounted at a 3% annual rate as per the guidelines of the Public Health Service Panel on Cost-Effectiveness in Health and Medicine. We will measure differences in hospital costs based on internal data warehouse cost data weighted by the Centers for Medicare & Medicaid Services Cost Report cost-to-charge ratio [26].

**Table 1 table1:** Elements included in health system decision analysis for artificial intelligence implementation.

Element	Example
ROI^a^	ROI = profit or cost, inclusive of costs related to clinical deterioration cases averted and costs related to unnecessary intervention (ie, false positives)
Capacity changes	C-score = (delta LOS^b^ in days x patients per week) + (added bed days/LOS of unit in days)
Staff training times	Average time to complete virtual cases per user group
Implementation costs	Costs associated with staff training or use of case-based approach
Impact on workforce	Number of false alarms as a unit of registered nurse time

^a^ROI: return on investment.

^b^LOS: length of stay.

#### Outcome Ascertainment and Event Adjudication

Numerical and categorical data (lab values, timestamps, room transfers, etc) will be extracted in bulk from the University of Virginia clinical data warehouse and uploaded into a Research Electronic Data Capture (REDCap) database for outcome analyses. For nonautomated outcome elements, such as suspicion of infection, emergent status of intubations, surgeries or transfers, suspicion of shock, actual shock, indications for vasopressors, and others, protocol-trained clinical research coordinators (consisting of registered nurses or medical doctors) will individually review the electronic medical records of case and control participants.

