## Methods

### Overall Design

We will be conducting a parallel, cluster randomized controlled trial (RCT). All patients who are admitted to an 85-bed acute care cardiology medical-surgical floor will be enrolled in the study. In June 2020, institutional review board approval was granted for the Predictive Monitoring-Impact in Acute Care Cardiology Trial (PM-IMPACCT) along with waiver of informed consent, given the minimal risk nature of the study protocol. Clusters will be defined by room number, and upon enrollment, patients will be assigned to either intervention (CoMET display) or usual care (standard of care). The intervention will consist of CoMET display and charting in electronic medical records, mention of CoMET score on rounds, and standard of care cardiorespiratory monitoring when ordered. Meanwhile, usual care will consist of standard of care cardiorespiratory monitoring when ordered and no CoMET score displayed, charted, or mentioned on rounds. The study period will be 20 months. This report follows the SPIRIT (Standard Protocol Items: Recommendations for Interventional Trials) reporting guideline [24].

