### Intervention Details

Data will be automatically collected electronically in real time for all patients (intervention and usual care) admitted to the randomized beds on the cardiology floor. The CoMET server is hosted within the hospital information technology environment and interfaces with the hospital interface engine to automatically gather clinical information, including numerical values in flow sheets, laboratory results, and continuous cardiorespiratory monitoring data [25]. For the intervention group only, the scores will then be displayed on monitors in real time and will be updated every 15 minutes.

Clinical research coordinators will routinely be present on inpatient rounding to bring up the web-based version of the CoMET display for the intervention arm and discuss relevant trends and answer questions about CoMET interpretation. Nurses will be asked to assess CoMET scores as part of routine vital sign collection. Every hour, the CoMET scores flow through directly to the electronic medical record vital sign flowsheet. Assessment protocol guidelines in response to CoMET scores on the intervention arm will suggest that if the CoMET score rises by 2 or more within a period of 3 hours, a nurse should assess the patient and consider alerting the nurse practitioner or resident physician caring for that patient. There is no direct clinical action or response mandated as a part of this RCT*.*

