### Randomization Process

The room and bed in which a patient is placed is based on standard of care. The rooms are being cluster randomized to either intervention or usual care. The assignment of patients to rooms will not be influenced by the randomization status of the room.

There will be 14 clusters containing an average of 4 rooms (6 beds) each, with the aim of maintaining balance across wards and units (intermediate care unit, transplant, or neither). Clusters will be rerandomized every 2 months following a replicated Latin square design within each stratum to ensure balanced treatment assignment within each time period and over the length of the study. Randomization will be performed using the randomization inference package in R (The R Foundation for Statistical Computing). The randomization will be masked until it is implemented every 2 months. Postimplementation, the randomization will not masked or blinded because it will be clear to anyone in the hall or central station which beds have a CoMET score displayed and which do not. Future randomization assignments will only be known by the study statistician (SR) and those technical personnel implementing CoMET at the time that randomization changes (MC).

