### Study Outcomes and Statistical Analysis

#### Primary Hypothesis

The primary hypothesis is that display of predictive analytics monitoring on acute care cardiology wards increases the number of hours free from clinical deterioration.

The primary outcome is the number of hours free from clinical deterioration (acute clinical events) within 21 days of admission. Hours of acute clinical events are defined as the time when one or more of the variables found in Textbox 1 occur. A maximum score will be 21 event-free days (504 hours). Patients who are discharged from the hospital prior to 21 days without an event will be counted as having 21 event-free days (504 hours). Patients who die during the admission will be counted as having 0 event-free days (0 hours). As an example, a patient who has an emergent ICU transfer on hour 26 of their admission will have 25 event-free hours. Patients will be censored (with no event observed) at the time of nonemergent ICU transfer (ie, for planned bronchoscopy), nonemergent surgery transfer, or other transfer (change in bed assignment) because a change in bed assignment can result in a change in randomization allocation (as carry over could occur in patients who have a display and then become “undisplayed”). We will conduct a randomized (formerly called “intent-to-treat”) analysis, in which all available data on all randomized participants are included for the primary end point comparison between intervention and usual care.

For the primary outcome (hours free of an acute clinical event), the primary analysis will employ a generalized estimating equation (GEE) with Poisson link. This model will be able to handle the multiple levels of correlation in the study design—patients within a cluster and potentially different intervention arms within a patient who has an event and then returns to the ward—as well as differences in the amount of time at risk for each patient that is censored.

Study outcomes by hypotheses.

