**Hypothesis 1 (primary study outcome)**
1. Hours free from the following:An emergent intensive care unit (ICU) transfer (emergent defined as urgent, unplanned) and ICU stayEmergent intubation (emergent is defined by clinician’s notes as a nonplanned procedure)Cardiac arrest, if prior to ICU transferDeathEmergent surgery prior to an ICU transfer (emergent is defined by clinician’s notes as a nonplanned procedure)

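### Emergent status, which feeds three of the five primary components, is judged from records that reveal the arm, so the call can differ by arm

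*Protocol article*

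**What the plan says.** All references are to the Protocol article.

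- **What is judged.** Outcome Ascertainment and Event Adjudication lists "emergent status of intubations, surgeries or transfers" among the elements that cannot be extracted automatically. For these, "protocol-trained clinical research coordinators (consisting of registered nurses or medical doctors) will individually review the electronic medical records of case and control participants".
- **What the record contains.** Under Intervention Details, "Every hour, the CoMET scores flow through directly to the electronic medical record vital sign flowsheet". Under Overall Design, usual care has "no CoMET score displayed, charted, or mentioned on rounds".
- **Who presents the display.** Under Intervention Details, "Clinical research coordinators will routinely be present on inpatient rounding to bring up the web-based version of the CoMET display for the intervention arm".
- **Masking.** Randomization Process states: "Postimplementation, the randomization will not masked or blinded because it will be clear to anyone in the hall or central station".
- **What emergent means.** The outcome textbox, Hypothesis 1, counts an "emergent intensive care unit (ICU) transfer (emergent defined as urgent, unplanned") and the ICU stay. For intubation and surgery, the same textbox takes the status from the clinician's notes.
- **What the label does.** Under Primary Hypothesis, an emergent ICU transfer at hour 26 leaves 25 event-free hours. For the alternative label, "Patients will be censored (with no event observed) at the time of nonemergent ICU transfer". Nonemergent surgery transfer is treated the same way.

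**The concern.** In an open trial, the main protection for an outcome that needs judgment is that the person judging does not know the arm. Here the stated procedures work against that. The record under review has CoMET rows in one arm and none in the other, and the reviewing role is the one that presents and explains the display.

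The call matters because it decides whether the same transfer or operation is a primary event or a censoring with no event. Three of the five primary components (ICU transfer, intubation, surgery) depend on emergent status. If the threshold for calling something emergent differs slightly between arms, patients move between event and no event, which could create or hide an effect on the primary outcome.

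**Working it through.** **Step 1. Reading the sections together.** The document gives no figure to reproduce on this point, so the first check is whether each link is stated.

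1. Emergent status is decided by coordinators from the electronic record (Outcome Ascertainment and Event Adjudication): stated.
2. That record carries the score in one arm only (Intervention Details; Overall Design): stated. Both the presence and the absence of the rows identify the arm.
3. Coordinators are also the role on rounds for the intervention arm (Intervention Details): stated for the role, not for individuals.
4. The label separates event from censoring for ICU and surgery transfers (Primary Hypothesis): stated. Nonemergent intubation is not named as a reason for censoring; it simply does not count as an event.
5. Room for judgment differs by component. ICU transfer has no criterion beyond urgent and unplanned, and no stated source. Intubation and surgery rest on the clinician's notes, which limits the reviewer, but those clinicians are themselves unmasked.

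**Step 2. How much relabelling would matter (illustration only).**

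Inputs from Sample Size, Power Analysis, and Attrition: 10,424 admissions, 11% dropout, final-analysis alpha .047.

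Assumptions:
- Event rate p of 3-10%. The article gives no primary-event rate. Its Introduction gives 5% or more for subacute illnesses in general.
- Design effect D of 1-2. No intracluster correlation is given.
- A two-sided test. The article does not state the sidedness of the primary test.
- No true effect.
- A share m of display-arm events is called nonemergent, and no usual-care events are.

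Number per arm: 10,424 × 0.89 = 9,277; 9,277 / 2 ≈ 4,639.

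Formulas: p₂ = p(1 − m); p̄ = (p + p₂)/2; SE = √[2 p̄(1 − p̄) D / 4,639]; z = (p − p₂)/SE. The chance of a significant result is approximately Φ(z − 1.986) + Φ(−z − 1.986), where 1.986 is the two-sided critical value for .047.

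Worked case, p = 5%, m = 10%, D = 1:
- Events per arm: 4,639 × 0.05 ≈ 232, of which about 23 are relabelled.
- p₂ = 4.5%, p̄ = 4.75%.
- SE = √[2 × 0.0475 × 0.9525 / 4,639] = 0.00442.
- z = 0.005 / 0.00442 = 1.13.
- Φ(−0.85) + Φ(−3.12) ≈ 0.197 + 0.001 ≈ 20%.

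The same calculation over the range:

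| Event rate | Design effect | 5% relabelled | 10% relabelled |
|---|---|---|---|
| 3% | 1 | 7% | 13% |
| 3% | 2 | 6% | 9% |
| 5% | 1 | 8% | 20% |
| 5% | 2 | 6% | 12% |
| 10% | 1 | 12% | 37% |
| 10% | 2 | 8% | 21% |

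With no relabelling the figure is 4.7% throughout. At a 5% event rate, 5% relabelled is about 12 patients.

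**Step 3. What the illustration leaves out.** It compares two proportions, whereas the planned analysis is a GEE on event-free hours with time at risk. It applies m to all events, but death and cardiac arrest are not named among the judged elements. If a fraction j of events is open to judgment and a fraction r of those is relabelled, then m = j × r, which is less than r. It models one direction only.

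**The case against.** The strongest case against is that much of this rests on silence. The ascertainment section is two sentences in a journal article. Masked extracts, double reading and allocation of reviewers may be set out in a full protocol or manual that is not shown, and their absence here is not in itself a fault. The article does not say that reviewers look at the flowsheet rows. For intubation and surgery the reviewer largely transcribes a label already in the notes.

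Most of this stands as a limit on the claim, but it does not remove it. The point does not depend on a missing masking step. It depends on procedures the article does state: charting in one arm only, review of that same record, and coordinators on rounds. An unseen step could reduce the exposure, but nothing shown indicates one.

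A reader might go further than the text allows in three ways:

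- *The same people do both tasks.* The article says only that the same role does.
- *Reviewers know the arm, and clinicians' notes mention the score.* The text supports that reviewers can tell the arm. It places scores in the flowsheet and on rounds, and says nothing about free-text notes.
- *The primary result will be biased toward the display.* No bias is demonstrated. Closer scrutiny of displayed patients could push the other way.

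The relabelling shares are assumptions with no source in the document, and the upper end of the range needs a high event rate and no clustering.

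**Conclusion.** The point holds as an avoidable exposure in how the primary outcome is ascertained, not as a demonstrated bias. As written, the people who decide emergent status can tell the arm from the record, and the decision feeds three of the five primary components. ICU transfer is the most exposed.

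Under the assumptions above, one-directional relabelling of 5% of display-arm events would raise the false-positive rate from 4.7% to about 6-12%, and of 10% to about 9-37%. These figures show that modest differences in labelling would be enough to matter. They do not estimate what will happen, and they overstate the impact because deaths are not judged items. The change is a cheap improvement rather than a correction without which the trial could not be interpreted.

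**What to change.** 1. Judge emergent status from a chart extract with the CoMET flowsheet rows and the room and bed numbers hidden.
2. Assign each chart to a coordinator who did not round on that patient.
3. Add a supportive sensitivity analysis of the primary outcome that counts every ICU transfer, intubation and surgery from warehouse timestamps, whatever its emergent status. Agreement with the primary analysis should not be a condition for claiming benefit.

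Cost: some work to prepare the extracts, a reallocation of reviewers and one further analysis. Randomization, the intervention and the sample size are unchanged.

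Limits: masked review does not remove bias already in notes written by unmasked clinicians, and only the sensitivity analysis addresses that part. The sensitivity analysis is itself diluted by planned transfers and procedures. It could miss a real benefit if the display turns emergent transfers into planned ones, which is why it should be supportive only.

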#### Sample Size, Power Analysis, and Attrition

We expect 11% of participants to drop out of the primary outcome because they will be in a room that switches the randomization arm at the time when rooms are rerandomized or because they will transfer rooms during their admission to a room of the opposite randomization or to a nonstudy room. We have accounted for this attrition in clinical trial planning and sample size considerations. The number of admissions to a room which will undergo cluster randomization is estimated to be 10,424. The study type 1 error rate will be set to 5% and the type II error rate to 20% (80% power). Additionally, an interim analysis will prespecified after half of the participants have completed their primary outcomes assessment. The interim analysis will use an O’Brien-Fleming spending function, giving nominal α values of .003 (interim) and .047 (final) for the 2 analyses. Should the primary outcome cross a stopping boundary at the interim analysis, the data safety monitoring board (DSMB) will have the option of stopping the study early.

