#### Secondary Hypothesis

The secondary hypothesis is that display of predictive analytics monitoring on acute care cardiology wards increases the number of hours free of clinical deterioration among those emergently transferred to the ICU.

We will use the Kaplan-Meier method or Cox proportional hazards regression curve to show post-ICU transfer event-free survival and hours free of the events listed in Textbox 1. The analysis comparison will employ a 1-sided clustered log-rank test (survival analysis) assuming proportional hazard rates.

For secondary outcomes measured as proportions (ie, yes-or-no outcomes) we will use GEEs with logit link and binomial distribution, and use negative binomial distribution for rare events. GEEs will allow the correct modeling of the clustering design and estimation of the intracluster correlation.

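### The final nominal level of .047 does not follow from the O'Brien-Fleming spending function named; with .003 at the halfway look it is .049

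*Protocol article*

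**What the plan says.** All of the relevant text is in the protocol article, Methods, Sample Size, Power Analysis, and Attrition.

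- Overall error: "The study type 1 error rate will be set to 5" percent, with 80% power.
- Timing: one interim analysis, "after half of the participants have completed their primary outcomes assessment".
- Boundary: "The interim analysis will use an O’Brien-Fleming spending function", "giving nominal α values of .003 (interim) and .047 (final) for the 2 analyses".
- Size: "The number of admissions to a room which will undergo cluster randomization is estimated to be 10,424".

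The article does not say whether the primary test is one-sided or two-sided. The only statement on sidedness is under Secondary Hypothesis, for a different endpoint: "The analysis comparison will employ a 1-sided clustered log-rank test (survival analysis) assuming proportional hazard rates".

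**The concern.** The two printed levels add up to exactly .05. Nominal levels from a group sequential boundary should add up to more than the overall alpha. The interim and final statistics share data and are positively correlated, so some of the trials that cross at the interim would also cross at the end, and that overlap is counted twice in the sum. A sum of exactly .05 suggests that .047 was obtained by subtraction.

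At stake is the decision threshold for the primary outcome. As written, the plan contains two rules: the threshold implied by the named method and the printed threshold. A final p-value between the two would be a success under one and a failure under the other. Settling that after the data are seen would look like a post hoc choice.

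**Working it through.** **Inputs.** Overall alpha .05, one look at half of the participants (taken as information fraction t = 0.5), an O'Brien-Fleming-type (Lan-DeMets) spending function, and printed levels .003 and .047, all from Sample Size, Power Analysis, and Attrition. Assumption: two-sided test; one-sided is checked below.

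**Step 1: the interim level.** The alpha spent per side by time t is α*(t) = 2[1 − Φ(z₁₋ₐ/₂ / √t)], with a = .025 per side.

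- z₀.₉₈₇₅ / √0.5 = 2.2414 / 0.7071 = 3.170
- α*(0.5) = 2[1 − Φ(3.170)] = .001525 per side, so .00305 two-sided (|Z₁| = 2.963)

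This reproduces the printed .003.

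**Step 2: the final level.** Under the null, Z₁ and Z₂ are bivariate normal with correlation √0.5 = 0.707. Solve for c in

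P(|Z₁| ≥ 2.963 or |Z₂| ≥ c) = .05.

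Numerical integration gives c = 1.969, a nominal two-sided level of **.0490**. The printed .047 is not reproduced. Holding the interim at exactly .003 also gives .0490.

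**Step 3: where .047 comes from.** .05 − .003 = .047. This is the probability, under the null, of crossing at the final look *without* having crossed at the interim. The corresponding nominal level is larger:

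| Pair | Overall type 1 error | Increment at final look |
|---|---|---|
| .003 / .049 | .04998 | .04998 − .003 = .0470 |
| .003 / .047 | .04801 | .04801 − .003 = .0450 |

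So an increment of .047 corresponds to a nominal level of .049. Using .047 as the nominal level spends only .045 at the final look.

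**Step 4: other readings.**

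| Version | Interim | Final |
|---|---|---|
| Spending function, two-sided .05 | .0031 | .0490 |
| Spending function applied to .05 without halving | .0056 | .0478 |
| Spending function, one-sided .05 | .0056 | .0482 |
| Classical O'Brien-Fleming, two-sided .05 | .0052 | .0480 |
| Classical O'Brien-Fleming, one-sided .05 | .0088 | .0467 |
| .003 fixed, one-sided .05 | .003 | .0493 |

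- If .003 is a rounded value (.0025 to .0035), the two-sided final level lies between .0492 and .0488.
- If the information fraction differs from 0.5, a final level near .047 needs t of about 0.63, where the interim level is about .0095.

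None of these gives .003 together with .047.

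**Step 5: size of the effect.** Take the drift (expected final Z) that gives 80% power with .003/.049; it is 2.807.

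- Power with .003/.047 at that drift: 79.5%.
- Information needed to restore 80% with .003/.047: a factor of 1.0125. Applied to the planned admissions, 10,424 × 0.0125 ≈ 130.
- Overall type 1 error if the test is one-sided: 4.78% instead of 4.80%.

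**The case against.** The spending function does produce .003 and .047 as the alpha *spent* at the two looks, so the sentence could be a correct split with the wrong label. That explains the number but does not rescue the text. The article calls the values nominal, which means the levels to which p-values are compared, and under a correct split the final comparison level is still .049.

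The error is also in the safe direction: 4.80% is below the 5% ceiling, so no protection against a false positive is lost. This stands, and it limits the weight of the point.

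The power comparison is conditional. The article does not say which alpha was used for sizing, gives no effect size or intracluster correlation, and presents 10,424 as an estimate of admissions, not as the output of a formula. If the trial was sized with .047, its power is 80% as stated. The 79.5% and the 130 admissions therefore apply only if sizing used .049. This also stands.

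Finally, half of the participants need not be half of the information in a clustered, rerandomized design. That is true, and it makes .049 specific to t = 0.5. It does not help .047, because no information fraction tried pairs it with .003.

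**Conclusion.** The point holds. Given the overall alpha, timing and boundary that the article states, the final nominal level is .049, not .047. The printed pair has an overall type 1 error of 4.80% (4.78% one-sided) instead of 5%. If the trial was sized with the correct boundary, power falls by about half a percentage point, equivalent to about 1.3% of the information.

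The consequence is small and conservative. It still matters because the number is the success threshold for the primary outcome and contradicts the method that is said to produce it. The result assumes t = 0.5 and standard independent-increment theory. The .049 does not depend on sidedness once .003 is taken as given; among the spending-function readings at t = 0.5, .003 itself arises only for a two-sided 5% test.

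**What to change.** Replace .047 with .049 as the final nominal level, in the protocol and wherever the SAP repeats it, before any final comparison by arm is seen. If the sponsor deliberately prefers the simple split of .05 into .003 and .047, keep the number but do not present it as the nominal level from an O'Brien-Fleming spending function, and acknowledge that it spends 4.8%.

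If not already in the SAP or the monitoring board's charter, a sentence there that the final level is recomputed at the information fraction actually reached would be useful; its absence from the article is not a fault.

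The cost is one number. Overall type 1 error stays at 5%, and no change to the sample size or conduct is needed.
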